## Abstract

**Introduction:**

In the work-up strategy for pulmonary embolism (PE) in the ED, the recently introduced YEARS rule allows the raising of the D-dimer threshold to 1000 ng/ml in patients with no signs of deep venous thrombosis and no hemoptysis and in whom PE is not the most likely diagnosis. However, this decision rule has never been prospectively compared to the usual strategy. Furthermore, it is unclear if the YEARS rule can be used on top of the Pulmonary Embolism Rule-out Criteria (PERC). We aim to assess the non-inferiority of YEARS compared to current guidelines to rule out PE among PERC-positive ED patients with suspicion of PE.

**Methods/design:**

The MODIGLIANI study is a multicenter, European, non-inferiority, cluster-randomized, two periods cross-over, controlled trial. Each center will be randomized for the sequence of two 4-month periods: intervention (MOdified Diagnostic Strategy: MODS) followed by control (usual care), or control followed by intervention with 1 month of “wash-out” between the two periods. In the control period, the threshold will be as usual (500 ng/ml for patients aged 50 years or younger and age × 10 for older patients). In the MODS period, the threshold of D-dimers to rule out PE will be raised to 1000 ng/ml if no item of the YEARS score is present or will remain unchanged otherwise. Patients will be included if they have a suspicion of PE, defined as chest pain, dyspnea, or syncope. Non-inclusion criteria comprise a high clinical probability of PE or PERC-negative patients with low clinical probability.

**Ethics and dissemination:**

The study has received the following approvals: Comité de protection des personnes Ile de France XI (France) and Comité de Ética de la Investigación con medicamentos del Hospital Clínic de Barcelona (Spain). Results will be made available to all included participants and other researchers.

**Trial registration:**

ClinicalTrials.gov, NCT04032769. Registered on 24 July 2019.

## Strengths and limitation of this study

This trial will address the safety of the YEARS rule applied in combination with PERC (i.e., after excluding PERC-negative patients) for the exclusion of pulmonary embolism in the emergency department.This trial will compare and assess the benefits of YEARS compared to the conventional strategy with age-adjusted D-dimers.This trial is a cluster cross-over randomized trial and is not randomized at the patient level.

## Background

The diagnosis of pulmonary embolism (PE) is a crucial matter in the emergency department (ED) [1]. The overall prevalence of PE in suspected patients continues to decrease, and the rate of diagnostic failure is now below 1% in Europe and the USA [2, 3].. Because a missed PE could be potentially lethal, several researches reported that PE is both over-investigated and over-diagnosed. The diagnostic gold standards for PE are the computed tomographic pulmonary angiogram (CTPA) and the V/Q scan, which have been shown to have clear risks (allergic reaction, acute renal failure, delayed solid tumor) and other downsides such as prolonged ED stay and increased cost [4–6]. To limit the use of imaging studies, two rules for excluding PE were recently reported to be safe: the PERC rule and the YEARS rule. PERC is an eight-item block of clinical criteria that has recently been validated to safely exclude PE in low-risk patients (Table 1). YEARS is a clinical rule that allows, in the absence of YEARS criteria, to safely raise the threshold of D-dimers to 1000 ng/ml for imaging studies (CTPA or V/Q scan) [7]. However, the latter has only been reported in prospective ED cohorts but has not yet been evaluated compared to the standard practice that follows international guidelines with the usual thresholds for D-dimers (e.g., 500 ng/ml for patients aged 50 years or younger and age × 10 ng/ml for older patients) [7–9]. Therefore, its added value in clinical practice remains uncertain. Furthermore, whether a modified diagnostic algorithm that combines these two rules could safely reduce imaging study use in the ED is unknown.

**Table 1 Tab1:** Pulmonary Embolism Rule out Criteria (PERC), 0–8, one point for each positive item

Age > 50 years	+ 1 point
Heart rate > 100	+ 1 point
SaO2 < 95%	+ 1 point
Unilateral leg swelling	+ 1 point
Hemoptysis	+ 1 point
Recent trauma or surgery	+ 1 point
History of PE or DVT	+ 1 point
Exogenestrogen use	+ 1 point

*DVT* deep venous thrombosis, *PE* pulmonary embolism

The MODIGLIANI study is a trial designed to assess the non-inferiority and cost-effectiveness of the modified diagnostic strategy (MODS) that combines YEARS and PERC for ruling out PE in the ED.

## Methods/design

### Study design

The MODIGLIANI study is a prospective, multicenter, non-inferiority, cluster-randomized, cross-over, controlled trial in 20 EDs in France and Spain. The complete protocol can be seen in the appendix (Supplementary file 1). The study start date was October 1st 2019 and the end of the recruitment period is estimated to be in June 2020 and study completion October 1st 2020.

Each center will be randomized for the sequence of the periods: intervention (MOdified Diagnostic Strategy (MODS)) followed by control (usual care), or control followed by intervention with 1 month of “wash-out” between the two periods. The participating centers will implement the first assigned strategy until a target number of consecutive patients is reached (half of the patients to be included in total, namely 350 patients in each strategy); in the cross-over phase, the centers will implement the second assigned strategy in a similar number of consecutive patients. The reporting of this study will follow the CONSORT statement extended to cluster randomized trials. The reporting of the trial protocol paper follows the SPIRIT recommendations (Figs. 1 and 2) [10, 11].

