### Sample size calculation

In the recent recommendations of the International Society of Thrombosis and Hemostasis on studies for PE diagnosis in the ED, it has been suggested that the maximum acceptable failure rate of a tested strategy should not exceed 1.85% [3]. The recent large European prospective cohort studies on PE diagnosis (PROPER, PERCEPIC, YEARS, ADJUST-PE) reported a failure rate of 0.1–0.5%. With an anticipated failure rate of 0.5% in the control group, a non-inferiority margin set at 1.35% (according to the ISTH recommendations so the upper bound of the 95% confidence interval (CI) of the failure rate in the intervention group will not exceed 1.85%), beta = 20%, and one-sided alpha = 2.5%, N1 = 857 patients are needed (East 6, Cytel, Cambridge, MA, USA). Under the assumption of an intra-class correlation coefficient (CCIC) of 0.018, an interperiod correlation (η) of 0.0115 (based on previous cluster randomized trials in French EDs) and a mean cluster size for one period (m) = 22 patients, the cluster design effect would be 1.37 [17, 20]. Considering 5% of non-evaluable patients, with 18 centers and two periods, 1234 patients are needed.

Besides the non-inferiority analysis, it is of utmost importance that the upper bound of the 95% CI of the failure rate of the tested modified diagnostic strategy remains below 1.85%, whatever the rate of the control group is. Our retrospective study reported an anticipated failure rate at 0.85% but focused only on low risk patients. Therefore, with an anticipated failure rate of 1% in the intervention period, the sample size of this group should be at least 700 to respect the maximal upper bound of 1.85%.

Therefore, for a conservative approach to these two conditions (non-inferiority margin at 1.35% and maximal upper bound of the 95% CI below 1.85%), 1400 (700 in each group) subjects will be needed in this study.

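### The article gives two unreconciled rules for when a centre crosses over (4-month periods or a patient count), and its cluster size of 22 does not fit its own totals

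*Protocol article*

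**What the plan says.** On the switch between strategies, the article makes two statements.

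- Abstract, Methods/design: "Each center will be randomized for the sequence of two 4-month periods", with a 1-month wash-out between them. No patient target is mentioned.
- Study design: centres apply the first strategy "until a target number of consecutive patients is reached". The target is given as "half of the patients to be included in total, namely 350 patients in each strategy". After that, "the centers will implement the second assigned strategy in a similar number of consecutive patients". No 4-month limit is mentioned.

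The same section puts the start at 1 October 2019 and says "the end of the recruitment period is estimated to be in June 2020".

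On numbers, the Sample size calculation section uses "a mean cluster size for one period (m) = 22 patients" to obtain a design effect of 1.37. It then states that "with 18 centers and two periods, 1234 patients are needed", and finally raises the total to 1400 (700 per group). The Study design section describes a "controlled trial in 20 EDs in France and Spain".

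The Statistical analysis plan section fits mixed models with a random centre effect, and with period and the strategy-by-period interaction as fixed effects.

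**The concern.** In a cluster cross-over trial the switching rule is part of the design. A calendar rule and a count rule coincide only if recruitment happens to deliver the target in exactly 4 months. The article does not cover the other two cases, in which 4 months pass before the target is met or the target is met early.

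The target also comes without a unit of action. Centres are told to continue until it is reached, but the only figure given is for the whole trial. A centre cannot tell from the article whether it switches on its own count, on the count of its sequence group or on the trial total.

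The choice affects the analysis. Under common calendar periods, period 1 and period 2 cover the same dates in both sequences, and a fixed period effect absorbs what changes between them. Under a count rule applied by centre or by sequence group, period 1 can end on different dates. The period label then no longer stands for one stretch of calendar time, and differences by season or calendar time may be only partly removed from the strategy comparison.

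A second inconsistency lies alongside the first. The cluster size per period feeds the design effect, but it does not agree with the number of patients per centre-period that the plan's totals require.

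**Working it through.** **1. The two switching rules side by side.**

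| | Abstract | Study design |
|---|---|---|
| What ends period 1 | 4 months elapsed | target number reached |
| Level at which it applies | each centre | centres, but the figure is trial-wide |
| If the other condition is met first | not stated | not stated |

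**2. What the figure of 350 means.** Half of 1400 is 700 patients in the first phase, or 350 under each strategy. Over two strategies and two periods, 350 × 2 × 2 = 1400, which matches the stated total. Read as a target for each centre, it would give 350 × 2 × 18 = 12,600 or 350 × 2 × 20 = 14,000 patients, so that reading is excluded. It is a trial-wide count per strategy per period.

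**3. The calendar.** 4 + 1 + 4 = 9 months from 1 October 2019 ends with June 2020, the stated end of recruitment. The recruitment window therefore fits the calendar rule.

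**4. The plan's own sample size.** The inputs from the Sample size calculation section are a failure rate of 0.5% in both groups, a margin of 1.35%, one-sided alpha of 2.5% and power of 80%.

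- Total before clustering: 2 × [2 × 0.005 × 0.995 × (1.960 + 0.842)² / 0.0135²] = 857. This reproduces N1 = 857.
- Design effect: 1 + (22 − 1) × 0.018 = 1.378. The stated 1.37 matches this form, which leaves out the interperiod correlation of 0.0115.
- Inflation: 857 × 1.37 / 0.95 = 1236, which reproduces the stated 1234 to within rounding.

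**5. Patients per centre-period implied by the totals.**

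- 1234 / (18 × 2) = 34.3
- 1400 / (18 × 2) = 38.9
- 1400 / (20 × 2) = 35.0
- In the other direction, 22 × 2 × 18 = 792 and 22 × 2 × 20 = 880. Neither is 1234 or 1400.

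**6. Design effect with a consistent cluster size.** With the stated interperiod correlation, the cross-over form is 1 + (m − 1) × 0.018 − m × 0.0115.

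| m | Without interperiod term | With interperiod term |
|---|---|---|
| 22 | 1.378 | 1.125 |
| 35 | 1.612 | 1.210 |
| 39 | 1.684 | 1.236 |

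**7. Does 1400 still suffice?** With 5% non-evaluable, 1400 × 0.95 / 2 = 665 evaluable per group. Power by the plan's normal approximation is Φ(0.0135 / √(2 × 0.005 × 0.995 / n) − 1.960), where n is the effective number per group.

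- m = 35: n = 665 / 1.210 = 550, power about 89%.
- m = 39: n = 665 / 1.236 = 538, power about 88%.

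The totals required for 80% power would be 857 × 1.210 / 0.95 = 1091 and 857 × 1.236 / 0.95 = 1115, both below 1400. If m were corrected but the interperiod term still left out, the required totals would be about 1454 (m = 35) and 1519 (m = 39), and 1400 would give about 78% and 77%. The two corrections therefore need to be made together.

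**The case against.** The strongest reply is that the two rules describe one plan. The recruitment window fits 4 + 1 + 4 months, so the patient number can be read as what each 4-month period is expected to deliver. The full protocol (Supplementary file 1) and Fig. 1, whose caption announces the numbers per period and strategy, are not available here and may give centre-level targets. The coding of period may be settled in the separate analysis plan. Randomization is stratified on country and center size, which works against one sequence recruiting systematically faster than the other. The requirement for consecutive patients limits any influence of physicians on the pace.

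Much of this stands. It makes the calendar reading the more plausible one and a large bias less likely. It does not remove the conflict, because the Study design section says in terms that reaching the number ends the first strategy. A supplement cannot make two different statements within the article agree.

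Two stronger readings are tempting.

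- A reader might infer that the calendar rule would recruit only 792 to 880 patients and leave the trial underpowered. The documents do not support this. The figure of 22 appears only as an input to the design effect and is nowhere given as the expected 4-month accrual of a centre. It already disagrees with the 1234 in its own paragraph. The 792 to 880 shows that the cluster size is inconsistent and is not a recruitment forecast.
- A reader might infer a definite seasonal bias under the count rule. The documents give neither recruitment speeds by sequence nor a time trend in any endpoint, so any figure would rest on invented inputs. Nor is misalignment certain: if the trial-wide total triggered one common switch, all centres would still change on the same date.

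**Conclusion.** The point holds as an inconsistency in the design description. The article states two switching rules, and does not say which governs or at what level the count applies. The consequence is conditional: if switching follows counts by centre or by sequence group, the fixed period effect need not fully adjust for calendar time. The size of any bias cannot be derived from the document.

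The cluster size of 22 is a separate, definite mismatch: the totals imply 34.3 (from 1234) or 35 to 39 (from 1400) per centre-period. Correcting it does not undermine the sample size, provided that the stated interperiod correlation is used. The design effect becomes about 1.21 to 1.24, and 1400 patients give about 88 to 89% power. This rests on the plan's own event rate, margin, correlations, 5% loss and normal approximation, and on equal cluster sizes. It concerns the non-inferiority condition only, not the separate requirement on the upper confidence bound in the intervention group.

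**What to change.** 1. State one switching rule, in the same terms, in the abstract and in the Study design section. The preferable rule is common calendar periods for all centres (4 months, 1-month wash-out, 4 months), which fits the October 2019 to June 2020 window. Present 350 per strategy per period as a trial-wide recruitment target and not as a trigger. If a count rule was intended, say at which level it applies and what happens when 4 months pass first.
2. The trial has been recruiting since October 2019, and the protocol version cited is dated 29 February 2020, when 4-month first periods would already have ended. So record the actual switch date of each centre, and add a sensitivity analysis that adjusts for calendar time as well as period.
3. Restate the mean cluster size per period so that it agrees with 1400 patients and with one stated number of centres (18 or 20). Recompute the design effect with the interperiod correlation, and show the formula.

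The cost is small: wording in three sections, a clarification to sites, one date per centre and one extra sensitivity model. On the calculation above, the target of 1400 does not need to change for the non-inferiority comparison.

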**Fig. 1 Fig1:**
[figure not shown]
Study flow diagram. Number of subjects needed in each period and strategy

**Fig. 2 Fig2:**
[figure not shown]
SPIRIT figure. *ED* emergency department, *PE* pulmonary embolism, *CTPA* computed tomographic pulmonary angiogram

### Selection of participants

This study will include patients who provide written or oral consent with a suspicion of PE defined as:
New onset of or worsening shortness of breathor chest pain,or syncope

As the prevalence of PE in patients with isolated syncope is not reportedly sufficiently low to rule out PE, we also included this inclusion criteria along with chest pain and shortness of breath [12].

Non-inclusion criteria are listed as follows:
Anticipated inability to be followed up at 3 monthsObvious cause other than PE for chest pain, syncope, or dyspneaHigh clinical probability of PE (estimated by the physician gestalt as > 50%)Low clinical probability of PE (estimated by the physician gestalt as < 15%) and no item of the PERC score (Table 1)Acute severe presentation (clinical signs of respiratory distress, hypotension, SpO2 < 90%, shock)Concurrent anticoagulation treatmentCurrent diagnosed thrombo-embolic event (in the past 6 months)PrisonersPregnancyNo social securityParticipation in another intervention trial

The emergency physician will assess the clinical probability of PE during screening, estimated by the clinician gestalt. As described in previous studies, this gestalt assessment is established by answering the question “How do you estimate the pre-test clinical probability: low, moderate, or high?” Patients with a high clinical probability of PE will not be included because they should be investigated with CTPA or V/Q scan, and therefore our modified algorithm will not concern them [13–15]. We will also exclude patients with a low clinical probability and a PERC score of 0 (based on clinical parameters taken by the emergency physician at the time of first clinical evaluation), as it has been validated that these patients have a very low risk of PE and should not be investigated for PE [16, 17].

In all participating centers, patients will be screened and recruited by the treating emergency physicians.

### Procedure and interventions

The diagnostic strategy for PE will first include a D-dimer analysis. The threshold for ruling out PE before ordering an imaging study will depend on the study period; in the control period, a positive D-dimer is defined as > 500 ng/ml in patients aged 50 years and younger, and as > age × 10 ng/ml for patients older than 50 years.

In the intervention period, the YEARS score will be assessed (Table 2). If the YEARS score is 0 (absence of any of the three items), a positive D-dimer is defined as > 1000 ng/ml. In other cases, the threshold will remain unchanged (> 500 ng/ml in patients aged 50 years and younger, and as > age × 10 ng/ml for patients older than 50 years).

**Table 2 Tab2:** YEARS rule, 0–3, one point for each positive item

Hemoptysis	+ 1 point
Clinical signs of DVT	+ 1 point
PE is the most likely diagnosis	+ 1 point

*DVT* deep venous thrombosis, *PE* pulmonary embolism

The total duration of a patient’s participation in the study is 3 months.

### Objectives and outcomes

The primary objective of this trial is to assess the safety of a modified diagnostic strategy (MODS) in the ED using the YEARS rule for patients in whom PE is not excluded by PERC score. Secondary objectives are to assess the efficacy of the MODS strategy in reducing ordering of CTPA or V/Q scan, introduction of anticoagulant, ED length of stay, hospital admission following ED visit, all causes readmission and mortality at 3 months, and diagnosed pulmonary embolism at 3 months after excluding isolated sub-segmental PE. The trial will also assess the safety of the PEPS score (Table 3) and evaluate the overall 3-month cost-reduction of the MODS strategy [18].

**Table 3 Tab3:** Pulmonary Embolism Probability Score (PEPS)

	Points
Age < 50 years	−2
Age 50–64 years	−1
Chronic respiratory disease	−1
Heart rate < 80/min	− 1
Chest pain and dyspnea	1
Prolonged decubitus	2
Sex male	2
Syncope	2
History of thrombo-embolic disease	2
Estrogen use	2
SpO2 < 95%	3
Lower leg pain or edema	3
Pulmonary embolism is the most likely diagnosis	5

< 0 Pulmonary embolism (*PE*) unlikely (PE ruled out) ; 0–4, low probability (D-dimer threshold at 1000 ng/ml) ; 5–11, intermediate probability (age-adjusted threshold for D-dimer) ; > 11, high probability (computed tomographic pulmonary angiogram indicated)

The primary endpoint is the failure proportion of the diagnostic strategy, defined as a diagnosed thrombo-embolic event at 3 months follow-up (either a PE or a deep venous thrombosis), among patients in whom PE was initially ruled out. Exclusion of PE in the ED is done upon a negative D-dimer result or negative CTPA or negative V/Q scan in both groups. The primary criterion of thrombo-embolic event will be based on an objective diagnosis of DVT on Doppler ultrasonography, an intraluminal defect on CTPA, or a V/Q lung scan with a reported high probability. To confirm the occurrence of the primary endpoint, all files with evidence of thrombo-embolic event collected by the local investigator of each center will be independently reviewed by an adjudication committee of three experts, emergency physicians, blinded one to each other, and blinded to the study period. The adjudication committee will also review cases of death with no evidence of thrombo-embolic event and will adjudicate the death as likely related to a PE or not. Adjudication of a PE-related death will follow the recommendations of Tritschler et al. [19]. The review process includes analysis of all medical files of the patient from inclusion to follow up, including reports of any imaging study.

Secondary endpoints include:
CTPA or V/Q scanAnticoagulant therapy administrationLength of stay in the ED (hours)Admission to the hospital following ED visitAll causes re-hospitalization at 3 monthsDeath from all causes at 3 monthsDiagnosed pulmonary embolism at 3-month follow-up, excluding the isolated sub-segmental pulmonary embolism, among patients in whom PE has been initially ruled outPulmonary Embolism Probability Score (PEPS)3-month total cost and cost-effectiveness (cost per major adverse event averted)

Details of PEPS are reported in Table 3 [18].

### Sample size calculation

In the recent recommendations of the International Society of Thrombosis and Hemostasis on studies for PE diagnosis in the ED, it has been suggested that the maximum acceptable failure rate of a tested strategy should not exceed 1.85% [3]. The recent large European prospective cohort studies on PE diagnosis (PROPER, PERCEPIC, YEARS, ADJUST-PE) reported a failure rate of 0.1–0.5%. With an anticipated failure rate of 0.5% in the control group, a non-inferiority margin set at 1.35% (according to the ISTH recommendations so the upper bound of the 95% confidence interval (CI) of the failure rate in the intervention group will not exceed 1.85%), beta = 20%, and one-sided alpha = 2.5%, N1 = 857 patients are needed (East 6, Cytel, Cambridge, MA, USA). Under the assumption of an intra-class correlation coefficient (CCIC) of 0.018, an interperiod correlation (η) of 0.0115 (based on previous cluster randomized trials in French EDs) and a mean cluster size for one period (m) = 22 patients, the cluster design effect would be 1.37 [17, 20]. Considering 5% of non-evaluable patients, with 18 centers and two periods, 1234 patients are needed.

Besides the non-inferiority analysis, it is of utmost importance that the upper bound of the 95% CI of the failure rate of the tested modified diagnostic strategy remains below 1.85%, whatever the rate of the control group is. Our retrospective study reported an anticipated failure rate at 0.85% but focused only on low risk patients. Therefore, with an anticipated failure rate of 1% in the intervention period, the sample size of this group should be at least 700 to respect the maximal upper bound of 1.85%.

Therefore, for a conservative approach to these two conditions (non-inferiority margin at 1.35% and maximal upper bound of the 95% CI below 1.85%), 1400 (700 in each group) subjects will be needed in this study.

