Since this is a non-inferiority study, analysis of the principal criterion will be performed on the per-protocol population (patients without major protocol deviation as no respect of selection criteria, no respect of strategy assigned by randomization, missing values for the principal criteria, or other major protocol deviation identified during data review before freezing of the data base). A sensitivity analysis will be performed on the intention-to-treat population (all randomized patients, except those that withdrew consent). Given the rare occurrence of a thrombo-embolic (TE) event, a generalized linear regression mixed model with Poisson distribution (log link) will be performed (Poisson model for proportions), taking into account a random effect for each center and considering period and strategy-by-period interactions as fixed effects. The decision rule will be based on the upper bound of the 95% two-sided CI of the incidence rates ratio of TE events. Any missing value will be considered as a failure. Secondly, sensitivity analysis will be performed using the 95% two-sided CI of the difference of percentage of TE events between groups. If the upper bound of the CI is above 1.35% of the difference, the inferiority hypothesis of the intervention group will be rejected. Secondary criteria will be compared between groups on the intention-to-treat population and under the superiority hypothesis. The proportions of irradiative imaging, of introduction of anticoagulation regimen, of hospital admission following the ED visit, of all causes of hospital readmission at 3 months, and of all-cause death at 3 months will be compared between groups by using generalized linear regression mixed models with Poisson distribution (log link), taking into account a random effect for each center and considering period and strategy-by-period interaction as fixed effects. If the number of events is sufficient, generalized linear regression mixed modeling with Bernoulli distribution (logit link) will be performed. The proportion difference between groups and its 95% CI will be calculated.

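### The 80% power at one-sided 2.5% behind the 857 (1234) patients rests on a normal approximation with about two events per arm; at 1400 patients, intervals that hold 2.5% give about 65–76%

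*Protocol article*

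**What the plan says.** In the protocol article, Sample size calculation, the non-inferiority comparison is sized on a risk difference: "With an anticipated failure rate of 0.5% in the control group", "a non-inferiority margin set at 1.35" percent, and then "beta = 20%, and one-sided alpha = 2.5%, N1 = 857 patients are needed". Clustering enters through an "intra-class correlation coefficient (CCIC) of 0.018", "an interperiod correlation (η) of 0.0115" and "a mean cluster size for one period (m) = 22 patients", with a stated design effect of 1.37. With 5% non-evaluable patients the total becomes 1234.

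A second condition follows: the upper confidence limit of the failure rate under the modified strategy must stay below 1.85%, which is said to need 700 patients in that group. Taking the two conditions together, the section concludes "1400 (700 in each group) subjects will be needed in this study".

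In Statistical analysis plan, the primary decision uses the confidence interval of an incidence rate ratio from a Poisson mixed model. The 1.35-point margin is applied in a sensitivity analysis using the "95% two-sided CI of the difference of percentage of TE events between groups". The article does not name the method for that interval.

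**The concern.** The article gives 857 patients as enough for 80% power at a one-sided error of 2.5%. At a 0.5% event rate that is about two events in each arm. A normal approximation to a difference of proportions is unreliable there: with very few events the estimated variance is small, the interval is too short, and the rule declares non-inferiority too often.

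The error level and the power are planning statements about a safety comparison, in which a false declaration of non-inferiority means accepting more missed thrombo-embolic events than the margin allows. If the two figures cannot both be true at the stated size, a reader cannot judge what an inconclusive result would mean. A reader could reasonably assume that raising the total from 1234 to 1400 leaves a comfortable reserve, so the check has to be made at 1400 as well.

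**Working it through.** **Inputs** (Sample size calculation unless noted): failure rate 0.5%; margin 1.35 points; 80% power; one-sided 2.5%; intra-class correlation 0.018; interperiod correlation 0.0115; 22 patients per cluster-period; design effect 1.37; 5% non-evaluable; 18 centers; 700 per group. Study design gives 20 departments. Equal rates of 0.5% in both arms are implied by the result, not stated.

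**1. Reproducing the plan's figures.** Unpooled normal formula, per arm:

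2 × 0.005 × 0.995 × (1.96 + 0.842)² / 0.0135² = 428.5, so 857 in total.

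Then 857 × 1.37 × 1.05 = 1233, or 857 × 1.37 / 0.95 = 1236, against 1234 stated. By its own method the arithmetic is right. Expected events per arm: 429 × 0.005 = 2.1.

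**2. Exact properties at 429 per arm.** All pairs of binomial counts were enumerated. Non-inferiority is declared when the upper limit of the two-sided 95% interval for the difference is below 1.35 points. Power is at 0.5% versus 0.5%; error is at 1.85% versus 0.5%.

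| Interval | Power | One-sided error |
|---|---|---|
| Wald | 77.8% | 4.4% |
| Newcombe | 57.4% | 1.7% |
| Score (Farrington-Manning) | 57.8% | 1.9% |

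The Farrington-Manning sample size formula asks for about 691 per arm (1381 in total) before clustering.

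**3. Design effects to consider at 1400.** The stated 1.37 is close to 1 + (22 − 1) × 0.018 = 1.378, which does not use the interperiod correlation. The cross-over form is 1 + (m − 1) × 0.018 − m × 0.0115:

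- m = 22: 1 + 0.378 − 0.253 = 1.125.
- m = 1400 / (20 × 2) = 35: 1 + 0.612 − 0.4025 = 1.21.
- m = 1400 / (18 × 2) = 38.9: 1 + 0.682 − 0.447 = 1.235, or 1.24 rounded.

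The stated m = 22 does not match 1400 patients, since 22 × 36 = 792. It is kept as the most favourable reading.

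**4. Power at 1400 after 5% loss.** Effective number per arm = 700 × 0.95 / design effect = 665 / design effect.

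| Design effect | Effective n per arm | Score and Newcombe power | Wald power (one-sided error) |
|---|---|---|---|
| 1.37 (stated) | 485 | 64.7% | 83.6% (4.3%) |
| 1.24 (m = 39) | 536 | 69.9% | 85.3% (4.0%) |
| 1.21 (m = 35) | 550 | 70.8% | 87.4% (4.0%) |
| 1.125 (m = 22) | 591 | 76.1% | 88.8% (3.9%) |

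The score and Newcombe results agree in every row, with error of 1.8–2.1% at 1.85% versus 0.5%. Because the counts are discrete, power moves by a point or so with small changes in n: the unrounded 1.235 gives 538 per arm and 71.5%.

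**5. Check on the effective-sample-size shortcut.** Clustered data were simulated with the stated correlations and a score interval widened by the design effect. Power was 66% at 1.37 and 72–73% at 1.20–1.22, within about two points of the table.

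**6. What 80% would take.** About 620–650 effective patients per arm with a score or Newcombe interval. None of the design effects above reaches that after 5% loss.

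**The case against.** **No printed figure is miscalculated.** This stands: 857 and 1234 reproduce, and by the same normal formula 1400 patients with 5% loss and a design effect of 1.37 have 84.6% power. The point is that the formula does not deliver the error and power it is quoted for, not that it was misapplied.

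**The article does not claim 80% power at 1400.** This also stands. A reader might infer such a claim, but beta = 20% is an input to 857, and 1400 follows from the single-arm precision condition. The calculation at 1400 shows only that the larger total does not repair the shortfall.

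**The article never commits to a Wald analysis.** A reader might infer that the trial will be analysed at an inflated error. The documents do not support that. The interval for the difference is unnamed and belongs to a sensitivity analysis, the primary rule is on the rate ratio, and the full analysis plan is not shown. What remains is that the only sized margin is the 1.35-point difference. For that comparison, a valid interval makes 80% too high and a Wald interval makes 2.5% too low.

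**Score and Newcombe are somewhat conservative here.** True, because the counts are discrete. An Agresti-Caffo interval has 74% power at 485 per arm, 79% at 536, about 80% at 550 and 83% at 591, but its error is 2.6–2.7% at 1.85% versus 0.5%, slightly above the stated level. Part of the gap is therefore the price of strict error control.

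**The 0.5% rate is the top of the 0.1–0.5% range that the article cites.** Correct. At 0.3% in both arms, Newcombe power is 79%, 80%, 85% and 89% at 485, 536, 550 and 591 per arm. The shortfall applies to the article's own planning rate, which is the rate its power statement uses.

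**More severe scenarios.** A reader might combine the 1% intervention rate with 0.5% in control and infer far lower power. The article uses 1% only for the single-arm bound, so that scenario is not part of its non-inferiority calculation. Losses from pulmonary embolism diagnosed at the index visit are not quantified in the article and are not used here.

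**Conclusion.** The point holds as a correction of stated planning properties. At 857 patients, 80% power and 2.5% one-sided error are not achieved together: about 78% power comes with 4.4% error, or 57–58% power with the error held. At 1400 patients the 1.35-point comparison has about 65–76% power under an interval that keeps the error at or below 2.5%. The position in that range depends on the design effect, and every reading is below 80%.

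This rests on equal 0.5% rates, exactly 5% loss, equal allocation, and clustering handled as an effective sample size, which the simulation supports. It says nothing about the power of the rate-ratio rule, for which the article gives no numerical margin. It does not show that the trial's analysis is invalid or that the 1400 is wrong for the precision condition that set it.

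**What to change.** In Sample size calculation, state the power of the 1.35-point comparison at 1400 patients as about 65–76% at equal 0.5% rates after 5% loss, with the design effect behind each end, under an interval that keeps one-sided error at or below 2.5%. Withdraw 80% power at 2.5% as the property of 857 and 1234, or label it as a normal-approximation figure that exact calculation does not confirm.

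In Statistical analysis plan, name a cluster-adjusted score or Newcombe interval for the difference in failure proportions, rather than a simple normal one. If the full analysis plan already specifies such an interval, a cross-reference is enough.

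The cost is wording in two sections and a less favourable stated power. No additional patients and no change in conduct are needed.
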